### Study overview

The EUC-CHF trial is an open-label, registry-based, prospective, single center study. It will recruit patients with severe acute decompensated HF who are hospitalized for HF worsening and significant weight gain due to overt fluid overload 24 h from hospital admission. The determination that acute decompensated HF is the primary cause of hospitalization will be made by the site’s principal investigator or sub-investigator, based on the assessment of the clinical signs and symptoms as well as laboratory examinations that lead to the admission. Patient enrollment should be completed and study treatment initiated within 24 h from hospital admission. Patients will be enrolled 1:1 sequentially to receive standard medical therapy (control group) or early UF (early UF group). Up to 2 doses of IV LDs will be allowed before enrollment.

The diuretic protocol adopted by our study in the control group refers to the protocol of AVOID-HF and CARRESS-HF trial as well as the dose recommended by the guideline according to patients’ vital signs, status of hemoconcentration, and renal function (Table 1) [10, 11]. Patients of the early UF group will be treated with a single or repeated session of UF within 24 h from admission (according to local clinical practice and with availability of nursing surveillance during UF) until the relief of patient’s symptom. The UF protocol adopted by our study also refer to the protocol of AVOID-HF and CARRESS-HF trial (Table 2).

[figure not shown]

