Inclusion criteria	1. Patient must be more than 18 years old. 2. Acute decompensated HF within 24 h of hospital admission. 3. Fluid overload, defined as edema of the lower extremities and at least 1 of the following: 1) elevated jugular venous pressure > 10 cm H_2_O, 2) pulmonary rales, paroxysmal nocturnal dyspnea or orthopnea, 3) pulmonary edema or pleural effusion on chest X-ray, 4) enlarged liver or ascites, 5) pulmonary wedge or left ventricular end diastolic pressure ≥ 20 mmHg, or 6) rapid increase of body weight ≥ 2 kg. 4. NYHA classification III-IV. 5. Patient is informed and has signed informed consent. Patient is willing to attend an outpatient follow-up.
Exclusion criteria	1. Acute coronary syndrome. 2. Severe mitral or aortic stenosis. 3. Severe renal insufficiency (serum creatinine ≥3.0 mg/dl or eGFR ≤ 30 mL/min). 4. Systolic blood pressure ≤ 90 mmHg or depending on high dose of vasoactive drug to maintain systolic blood pressure ≥ 90 mmHg. 5. Hematocrit > 45%. 6. Unattainable venous access. 7. Comorbidities expected to prolong hospitalization. 8. Contraindications to anticoagulation. 9. Serious bleeding in the last 6 months (this includes, but is not limited to, prior intracranial hemorrhage, active peptic ulcer disease, active internal bleeding, bleeding at a noncompressible site). 10. Hematuria within 30 days before randomization. 11. Patients at high risk of bleeding (this includes, but is not limited to, clinically significant thrombocytopenia or anemia, platelet count < 90,000/μL at screening or pre-randomization, anemia of unknown cause with a hemoglobin level < 10 g/dL at screening or pre-randomization, coagulation disorders, recent stroke within past 30 days, documented hemorrhagic tendencies, or blood dyscrasias). 12. Uncontrolled hypertension (> 180/110 mmHg). 13. Severe infection. 14. Use of iodinated radiocontrast material. 15. Participation in another controlled clinical trial, either within the past 2 months or still ongoing. 16. Women who are pregnant, breast-feeding, or of child-bearing potential. 17. Patient who is mentally ill.

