**Fig. 1 Fig1:**
[figure not shown]
Study design. The control group will be treated with intravenous loop diuretics by experienced HF cardiologists according to guideline recommendations. Patients of the early UF group will receive a single or repeated session of UF started within 24 h from admission until the relief of patient’s symptom. HF, heart failure; UF, ultrafiltration

The trial aims to recruit 40 patients (20 patients for each group) over an estimated 24-month period. After baseline visit, follow-up visit will occur at the end of study treatment, 24 h, 48 h, and 72 h after the end of study treatment, at discharge, and 30 days after discharge. At the baseline visit, informed consent will be taken, and additional baseline variables including gender, age, height, weight, occupation, race, physical activity, complete medical history (including history of smoking and drinking, past and present medical history, concomitant disease), vital signs, NYHA classification, dyspnea severity score, score by Minnesota Living with Heart Failure Questionnaire (MLWHFQ) functional capacity, physical examination including distention of jugular vein, edema of lower extremity and congestion of other organs, laboratory test, electrocardiogram, chest X-ray, echocardiographic data and concomitant drug used up to 3 months before enrollment will be recorded.

Questionnaires (dyspnea severity score and score by MLWHFQ functional capacity) at follow-up visits will also be collected by trained clinicians. This will aid in our assessment of patients’ cardiac function and other safety data.

During follow-up, we will record all the primary and secondary end points and adverse events. All adverse events will be evaluated according to severity, causality, expectedness, and relationship to study treatment. Subjects who develop complications that, in the judgment of principal investigator or sub-investigator, are not suitable to continue the trial will be screened out from the study. Participants will continue with follow-up and may restart study protocol if the clinical situation resolves. Investigators are responsible for the decision to resume the study. If treatment according to the study protocol is clinically insufficient, the study will be suspended and effective treatment should be applied according to the current clinical practice.

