### Study outcomes

The primary end points of EUC-CHF are the changes of weight loss and dyspnea severity score at every scheduled visit which are considered as the part of a single composite endpoint, as well as the occurrence of clinically major bleeding defined by TIMI or GUSTO criteria [12].

Secondary outcomes include: net fluid loss, length of stay in CCU or ICU, change of score by MLWHFQ functional capacity, change of serum and ultrafiltrate concentrations of endotoxin, ET-1, TNF-a, IL-6 and IL-10, changes of cardiac function (the NYHA classification), changes in N-terminal proB-type natriuretic peptide (NT-proBNP) level, changes of LDs dose, HF rehospitalizations for congestive HF in 30 days after discharge, cardiovascular death and all-cause death in 30 days after discharge, change of blood pressure, changes in hepatic and renal function (serum creatinine concentration, estimated glomerular filtration rate [eGFR]), serum electrolytes, hemoglobin and incidence of acute coronary syndrome at scheduled visits.

Weights will be obtained at every scheduled visit using the same balance with the patient shoeless in a hospital gown after emptying the bladder. Weight loss is the difference between weight at baseline and the weight recorded at subsequent visits.

The dyspnea severity score by a proposal to standardize dyspnea measurement in clinical trials of acute heart failure syndromes by International Working Group on acute heart failure of European Society of Cardiology is used for the assessment of dyspnea [13].

Total fluid intake and output (ultrafiltrate and urine) measured at every scheduled visit after enrollment will be used to calculate net fluid losses.

Glomerular filtration rate will be calculated according to the abbreviated Modification of Diet in Renal Disease (MDRD) equation [14].

Acute coronary syndrome includes unstable angina, ST segment elevated myocardial infarction and non-ST segment elevated myocardial infarction. Myocardial infarction is defined according to the fourth universal definition of myocardial infarction [15]. Death will be considered cardiac according to the 2014 ACC/AHA key data elements and definitions for cardiovascular endpoint events in clinical trials [16].

We also will collect all the urine output after patients are enrolled to receive standard medical therapy or early UF until 72 h after the end of study treatment. Then we will measure the average urine electrolytes for every enrolled patient.

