### Statistical analysis

We will compare estimates of patients who receive UF therapy with those who receive conventional pharmacologic therapy. Concomitant medication and other baseline characteristics will be utilized in subgroup analysis.

Continuous variables will be summarized using descriptive statistics. Qualitative variables will be summarized by counts and percentages.

We will compare baseline characteristics. T-test or sign rank test will be used after testing for normality. Chi-square or Fisher’s exact test will be performed for categorical variables.

The primary efficacy endpoint (change of weight loss and dyspnea severity score) will be analyzed by Kaplan-Meier method, and comparisons between two groups will be performed using a log-rank test. Hazard ratio with 95% CI will be derived by the Cox proportional hazards model. Subgroup analyses of the efficacy endpoint are performed for the evaluation of impact of major clinical features on the improvement of primary efficacy endpoints by early UF therapy. Specific information is as follows:

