Although theoretically UF specific filter membrane could only penetrate small molecules such as sodium and water, there is no previous evidence from clinical studies on whether UF could filter out inflammatory mediators. It is not exactly certain whether UF is able to remove inflammatory mediators. Previous research found that high-volume continuous veno-venous hemofiltration combined with periodic filter change, different UF rates, different membrane pore sizes, different types of membrane, and different species were all related to the efficacy of removing inflammatory mediators by hemofiltration [34–36]. The capacity of filtering out mediators by UF specific filter membrane is influenced by many factors, such as pore size, screening coefficient of the membrane, molecular charge and molecular weight of the mediators. It is difficult to determine whether they can be filtered out only by the molecular weight of the mediators alone. Therefore, we will measure changes of serum and ultrafiltrate concentrations of inflammatory mediators including endotoxin, endothelin-1 (ET-1), tumor necrosis factor- (TNF-a), interleukin-6 (IL-6) and IL-10 in our study. We try to find out whether UF could relieve both fluid overload and other clinical manifestations such as HF related multiple organ dysfunction syndrome (MODS) in acute HF by filtering out certain inflammation mediators. Our study will provide further data regarding the ability of UF to filter out inflammation mediators. To our knowledge, this is the first trial exploring the effects of UF on circulating inflammatory mediators.

The present study is mainly limited by its open-label design and patient selection bias cannot be excluded, which will make the interpretation of the results somewhat limited. Also, the follow-up period is relatively short in our trial. Postpone the last clinical evaluation at 90 days and at an even later time point may provide more information of the advantages or disadvantages of UF.

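### The primary efficacy comparison is an unadjusted log-rank test, and the baseline dyspnea score, recorded in every patient, has no stated role as a covariate in a 40-patient trial

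*Protocol article*

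**What the plan says.** All references are to the protocol article.

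- **Size.** "The trial aims to recruit 40 patients (20 patients for each group) over an estimated 24-month period" (Study overview, text after Fig. 1). No power, effect size, SD or event count accompanies this number.
- **Baseline data.** The baseline visit records weight and, among other items, "vital signs, NYHA classification, dyspnea severity score" (same place).
- **Endpoint.** Under Study outcomes, the efficacy part of the primary endpoint is weight loss and change in dyspnea score at all scheduled visits, treated as one composite. For weight, "Weight loss is the difference between weight at baseline and the weight recorded at subsequent visits". The dyspnea score is defined by citation only, so its range and direction do not appear in the article.
- **Primary analysis.** Under Statistical analysis, the efficacy endpoint goes to Kaplan-Meier curves, and the two groups are compared by a log-rank test. Then: "Hazard ratio with 95% CI will be derived by the Cox proportional hazards model". No covariate is named for that model and none is ruled out.
- **Role of baseline data.** The same section compares baseline characteristics between groups and otherwise assigns them to subgroup analysis, through a stratified Cox model. The listed subgroup factors include weight and NYHA class but not the baseline dyspnea score.
- **Allocation.** "Patients will be enrolled 1:1 sequentially to receive standard medical therapy (control group) or early UF (early UF group" (Study overview). Table 3, however, has an exclusion worded "Hematuria within 30 days before randomization", and the Discussion concedes that "patient selection bias cannot be excluded".

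**The concern.** A change score does not remove the influence of the starting value unless baseline and follow-up are almost perfectly correlated. A patient who starts high tends to fall further than one who starts lower, whatever the treatment. With 20 patients per group the mean starting dyspnea will often differ, and an unadjusted comparison passes part of that difference into the treatment estimate. It also leaves in the error term variation that the baseline score could explain.

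The trial records the variable that would deal with both, yet fixes a primary test that cannot use it. The planned baseline comparison would reveal an imbalance, but the article states no step that acts on it. At stake are some power and the credibility of the dyspnea estimate if the groups start at different levels.

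**Working it through.** **Inputs from the article:** 20 per group; two-sided 0.05; six follow-up visits (end of treatment, 24, 48 and 72 h later, discharge, 30 days after discharge). **Not given, hence assumed:** the correlation rho between baseline and follow-up score (0.3, 0.5, 0.7 for dyspnea; 0.95 to 0.98 for weight), equal variances at both times, and any event definition. Power uses the normal approximation.

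**1. What 40 patients can detect.** The sample size comes with no inputs, so it cannot be reproduced, only solved backwards. Standardized difference for 80% power: (1.960 + 0.842) × √(2/20) = 0.886 (1.03 for 90%). As a hazard ratio, exp(−2 × 2.802/√E): 0.41 if all E = 40 patients have an event, 0.36 with 30 and 0.29 with 20. Only large effects are within reach.

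**2. Baseline imbalance under true randomization.** The SD of the difference in baseline means is √(2/20) = 0.316 score SDs. A difference above 0.3 SD has probability 34%, and above 0.5 SD 11%; the median absolute difference is 0.674 × 0.316 = 0.21 SD. A baseline difference D shifts the unadjusted difference in change by (1 − rho) × D in size. For D = 0.5:

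| rho | shift (score SDs) | SD of change, √(2(1 − rho)) | detectable effect, 0.886 × SD of change | shift / detectable effect |
|---|---|---|---|---|
| 0.3 | 0.35 | 1.183 | 1.048 | 33% |
| 0.5 | 0.25 | 1.000 | 0.886 | 28% |
| 0.7 | 0.15 | 0.775 | 0.686 | 22% |

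**3. Efficiency on the continuous score.** In units of the score variance, the change score has variance 2(1 − rho) and ANCOVA 1 − rho². The ratio is (1 + rho)/2, multiplied by 1 + 1/36 for estimating one covariate slope with 40 patients. Power is Φ(2.802/√ratio − 1.960) for an effect with 80% power unadjusted.

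| rho | ratio | after covariate cost | power | adjusted N matching 40 unadjusted |
|---|---|---|---|---|
| 0.3 | 0.65 | 0.67 | 93% | 27 |
| 0.5 | 0.75 | 0.77 | 89% | 31 |
| 0.7 | 0.85 | 0.87 | 85% | 35 |

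**4. The same question in a Cox model.** Simulation of 1,000 trials per setting, 20 per group, six visits, Efron ties, with an assumed log hazard of improvement linear in the latent change and a treatment effect of 1 score SD.

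| rho | power, unadjusted → adjusted | mean SE of log HR | mean log HR |
|---|---|---|---|
| 0.3 | 37.2% → 41.8% | 0.354 → 0.365 | 0.59 → 0.65 |
| 0.5 | 45.7% → 49.0% | 0.353 → 0.364 | 0.66 → 0.70 |
| 0.7 | 54.2% → 56.6% | 0.352 → 0.362 | 0.74 → 0.77 |

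The gains are 4.6, 3.3 and 2.4 points. They come from a less attenuated estimate; the standard error does not fall. With no treatment effect, the unadjusted log HR moved by 0.54, 0.34 and 0.29 per 1 SD of baseline imbalance at the three values of rho, and by at most 0.12 after adjustment. Unadjusted rejection under the null, including a run at rho 0.95, was 3.5% to 5.3%.

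**5. Weight.** At rho 0.95 the ratio after the covariate cost is 0.975 × 1.028 = 1.00, and at 0.98 it is 0.99 × 1.028 = 1.02. A 0.5 SD imbalance shifts the change by only 0.01 to 0.03 SD. Subtracting baseline already does the work.

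**The case against.** The strongest reply is that an unadjusted log-rank test is valid and widely used, so adjustment is a preference about efficiency. Chance imbalance is already part of the sampling variance, and the simulation confirms that type I error is not inflated. That stands: a reader might infer that the planned test gives invalid p values, and it does not.

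A reader might also infer that the Cox model contains treatment alone. The article does not say so. A covariate list is commonly left to the full protocol or analysis plan, so silence on it is no defect. The firm ground is the log-rank test, which is stated, and the stated destination of baseline data.

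It is tempting to apply the ANCOVA gains to the planned analysis. They compare two analyses of the continuous score, neither of which is planned; within a Cox model the gain is a few points. A floor effect in mildly breathless patients is also tempting to add, but the score's range is not given and entry requires NYHA class III or IV, so it cannot be checked.

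Finally, adjustment needs something to adjust. The composite has no separate dyspnea model, no single visit is chosen and no event is defined. This is correct and makes the fix longer than one added covariate, but it does not remove the case for adjusting.

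**Conclusion.** The point holds for dyspnea. The article fixes an unadjusted primary comparison and sends baseline data to subgroup analyses, while the baseline dyspnea score has no stated use beyond calculating change and describing the groups.

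On assumed correlations of 0.3 to 0.7 and equal variances, a baseline-adjusted analysis of the continuous score would raise 80% power to between 93% and 85%. It would also remove a shift of 0.35 to 0.15 score SDs for each 0.5 SD of baseline difference. In a Cox model the gain is about 2 to 5 points under one assumed event model, and the main benefit is protection against imbalance. For weight there is no material gain.

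The imbalance need not be chance alone. Enrolment is sequential and selection bias is conceded, while Table 3 speaks of randomization; these statements must be reconciled. If differences are systematic, adjusting for one score deals with them only in part, so it should not be presented as a cure for selection bias.

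**What to change.** In the Statistical analysis section, make the primary dyspnea analysis a comparison of the continuous score at one named visit, adjusted for the baseline dyspnea score (ANCOVA). This also removes the need for an undefined event in that component.

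If a time-to-improvement event is defined and kept, include the baseline dyspnea score in the Cox model that gives the primary hazard ratio. Note there that the adjusted hazard ratio is conditional on baseline, so it need not equal the unadjusted one even in balanced groups. Keep the unadjusted result as a sensitivity analysis in either case. Baseline weight need not be added for precision.

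Cost: one degree of freedom and no new data, since the score is already collected, and the planned software can fit either model. The dyspnea component must be separated from the composite and its visit named.

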**Discussion:**

EUC-CHF trial was primarily designed to evaluate the efficacy and safety of early UF in patients with acute decompensated HF to reduce volume overload and improve clinical outcome. The trial aims to determine if early UF in acute HF is superior to IV LDs in clinical parameter improvement without adverse events and prevents rehospitalization up to 30 days. Also the trial is expected to establish a scoring system based on Chinese population to guide early UF treatment in appropriate patients. EUC-CHF is one of the first controlled trials tailored to determine the benefit of UF with 24 h from hospital admission.

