The ability to predict the therapeutic effect of UF by patients’ individual characteristics as well as systolic blood pressure, heart rate, severity of edema, renal and hepatic function, NYHA classification, left ventricular ejection fraction, chamber diameter, concomitant disease and medication;The influence of different patients’ individual characteristics including gender, age, height and weight on the effect of UF for fluid removal and alleviation of dyspnea;The influence of baseline systolic blood pressure and heart rate on the effect of UF for fluid removal and alleviation of dyspnea;The influence of baseline severity of edema (i.e., edema of lower extremity and congestion of other organs) on the effect of UF for fluid removal and alleviation of dyspnea;The influence of baseline renal and hepatic function on the effect of UF for fluid removal and alleviation of dyspnea;The influence of different baseline cardiac function (including NYHA classification and left ventricular ejection fraction) on the effect of UF for fluid removal and alleviation of dyspnea;The influence of different baseline chamber diameter on the effect of UF for fluid removal and alleviation of dyspnea;The influence of different baseline concomitant disease on the effect of UF for fluid removal and alleviation of dyspnea;The influence of different concomitant medication on the effect of UF for fluid removal and alleviation of dyspnea;

Subgroup analysis of primary efficacy endpoint will be estimated using a stratified Cox model. The subgroup analysis will be tested by chi-square or Fisher’s exact tests.

The primary safety endpoints and secondary endpoints will be presented by summary statistics, as number of patients, event counts and percentage, variable counts and percentage.

All comparisons will report *p* values on the basis of 2-sided tests, and a p value ≤ 0.05 will be considered statistically significant. All statistical analyses will be performed using SPSS Statistics version 22 software.

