Currently, clinical UF use differs greatly among different centers, countries and physicians due to widely accepted consensus or guidelines. Bagshaw SM et al. proposed an algorithm aimed to evaluate when to initiate RRT. The algorithm included some patient-related factors, which may influence the time point of initiating RRT [23]. Equally, a clinical scoring system that is based on the patient’s clinical and laboratory information on admission as well as other potential risk factors obtained from present available trials may be useful for screening out patients suitable for UF. Using this system probably contribute to avoid unnecessary risks of UF. Amir Kazory et al. suggested a number of potential factors such as the primary renal structural disease, age, ejection fraction, blood pressure, serum sodium level, BNP level, presence of right-sided HF, history of LD resistance in previous hospitalizations, and progression of congestion despite high-dose LDs may be used as predictors for the responders from UF [24]. So our study will record baseline characteristics for subgroup analysis. We expect to find the risk factors associated with the non-responsiveness to UF. Also, we try to seek out certain patient-based clinical and laboratory parameters that could help to screen out patients appropriate for early UF.

Although experts and previous evidence from several randomized trials support the view that early UF resulted in more body fluid depletion, the timing of UF in acute HF patients in most trials are not considered as a risk factor [25]. It is not certain when and for which population is suitable to start UF. Further studies are needed to determine the clinical significance of timing for UF. So far there is no such research in China. In the present study, we will analyze the efficacy of early UF (within 24 h after admission) versus conventional pharmacologic therapy in Chinese patients with severe decompensated HF who are hospitalized for HF worsening and overt fluid overload. Thereafter, we hope to establish a scoring system based on Chinese population with acute decompensated HF to screen out appropriate candidates for early UF with the purpose of achieving better volume depletion and clinical outcome improvement. The scoring system may consist of the timing of UF as well as certain patient-based clinical and laboratory parameters.

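### The subgroup section asks how baseline factors change the effect of UF, but a stratified Cox model and chi-square or Fisher tests do not answer that, and 40 patients cannot support the expected scoring system

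*Protocol article*

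**What the plan says.** The Statistical analysis section says that the subgroup work is meant to show how major clinical features affect the improvement brought by early UF. It lists nine items. Nearly all ask about the influence of a baseline characteristic on what UF achieves for fluid removal and for dyspnea.

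Two methods are named for this. For estimation: "Subgroup analysis of primary efficacy endpoint will be estimated using a stratified Cox model". For testing: "The subgroup analysis will be tested by chi-square or Fisher’s exact tests". No treatment-by-factor interaction or heterogeneity test is mentioned. The significance rule is general: "All comparisons will report *p* values on the basis of 2-sided tests, and a p value ≤ 0.05 will be considered statistically significant".

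The Discussion part of the abstract says that "the trial is expected to establish a scoring system based on Chinese population to guide early UF treatment in appropriate patients". The main Discussion is softer and only hopes to establish such a score, but it says that baseline characteristics are recorded for the subgroup analysis and expects to find risk factors for non-response to UF. It adds: "The scoring system may consist of the timing of UF as well as certain patient-based clinical and laboratory parameters". On size, the Study overview states: "The trial aims to recruit 40 patients (20 patients for each group) over an estimated 24-month period".

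**The concern.** The question is one of effect modification: is the UF-versus-diuretic contrast larger in some patients than in others? The methods named answer different questions.

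- Stratifying a Cox model on a factor lets the baseline hazard differ between its levels but forces the treatment hazard ratio to be the same in all of them. The factor is adjusted away rather than examined.
- A chi-square or Fisher test compares proportions in a table. Run within each subgroup, it gives a set of separate p values, and a significant result in one level beside a non-significant result in another is not evidence that the effects differ.

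These results are meant to feed a tool for choosing who should receive an invasive, anticoagulated procedure. If the plan is followed literally, real differences can be missed and chance ones picked out. The small sample then makes the promised score unattainable even with the right test.

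**Working it through.** The article gives no power, effect size or event rate behind the figure of 40, so there is no sample-size derivation to reproduce. The checks below start from the stated design.

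**Inputs from the article.** 40 patients, 20 per group; 1:1 allocation ("Patients will be enrolled 1:1 sequentially to receive standard medical therapy (control group) or early UF (early UF group"); two-sided 0.05; effect measure for the primary efficacy endpoint: "Hazard ratio with 95% CI will be derived by the Cox proportional hazards model".

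**Inputs that are assumptions or readings.**
- The factor count is 14: gender, age, height, weight, systolic pressure, heart rate, edema, renal function, hepatic function, NYHA class, ejection fraction, chamber diameter, concomitant disease, concomitant medication. The last two are counted once each.
- The number of events is not given, so 40, 30 and 20 are shown.
- Each factor is split into two equal subgroups.

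**1. What the stratified model returns.** Simulation with 40 patients, all with events, in two subgroups (1,500 runs). With true hazard ratios of 0.5 in one subgroup and 2.0 in the other:
- the Cox model stratified on the subgroup gave an average hazard ratio of 1.00, significant in 2.9% of runs;
- the same model with a treatment-by-subgroup term detected the difference in 57% of runs.

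With a hazard ratio of 2 in both subgroups, the interaction test rejected in 4.8% of runs, close to its nominal level. So two strong opposite effects vanish under the stated model.

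**2. Multiplicity.** Chance of at least one false positive in k independent tests = 1 − 0.95^k.
- One endpoint, 14 factors: 1 − 0.95^14 = 0.51, with 14 × 0.05 = 0.7 false positives expected.
- Two outcomes, 28 tests: 1 − 0.95^28 = 0.76, with 28 × 0.05 = 1.4 expected.

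**3. What an interaction term could detect.** With d events, equal arms and equal subgroups, the variance of the log hazard ratio is 4/d, and that of the log ratio of two subgroup hazard ratios is 16/d. With 1.96 + 0.84 = 2.80 for 80% power, the detectable ratio of hazard ratios is exp(2.80 × √(16/d)).

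| Events | Detectable ratio of HRs |
|---|---|
| 40 | exp(2.80 × 0.632) = 5.9 |
| 30 | exp(2.80 × 0.730) = 7.7 |
| 20 | exp(2.80 × 0.894) = 12.3 |

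For comparison, the overall treatment effect at 40 events has 80% power for exp(2.80 × √(4/40)) = 2.43.

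With 40 events, power for a ratio of hazard ratios of 2, 3 or 4 is 19%, 41% or 59%. Events needed for 80% power, 16 × 2.80² / (ln ratio)², are 262, 105 and 66 respectively. The last two lines of evidence agree: the simulated case has a ratio of 4, where the formula gives 59% and the simulation 57%.

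**4. Timing of UF.** The Study overview requires treatment to start within 24 h of admission, and the only comparator is drug therapy. Start times can vary between 0 and 24 h, but nobody is assigned to UF beginning later.

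**The case against.** **Kinder readings of the methods.** A stratified Cox model can carry an interaction term, and the word may be loose shorthand for fitting the model separately in each subgroup. Chi-square could mean a heterogeneity test. Interaction details are often left to an analysis plan. These points soften the criticism but do not remove it. No interaction term is named; separate fits still leave the difference between hazard ratios untested; and pairing chi-square with Fisher's exact test points to contingency tables. The article states a rule, and the rule does not fit the question, so this is not a matter of omitted detail.

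**Multiplicity.** The Study outcomes section treats weight and dyspnea as one composite, so 14 tests are as fair a count as 28, and several factors (height with weight, NYHA class with ejection fraction) are plainly correlated. This stands: 51% to 76% is a range, and independence puts it on the high side.

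**Stronger readings the article does not support.**
- A reader might infer that the score will be fitted in the 20 UF patients alone. No section says so. The Statistical analysis section sets a comparison of both groups, and the Discussion's idea of a score also draws on risk factors from other trials. A calculation of overfitting for a 14-predictor regression in 20 patients would describe a model nobody has planned.
- A reader might infer that timing is a fixed component of the score. The text says only that it may be one, and the same paragraph calls for further studies on timing.
- A reader might infer that chance findings will be presented as a selection tool. The main Discussion speaks of hoping and trying, and the authors concede limits to interpretation. Only the abstract is firm.

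**Conclusion.** The point holds as a mismatch between question and method, together with an abstract claim that the sample cannot bear. Followed as written, the stratified Cox model and the chi-square or Fisher tests do not show whether the UF effect varies with any factor.

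Correcting the method does not rescue the scoring system. The ratio of 5.9 is a best case, since it assumes an event in all 40 patients and an even split; fewer events or uneven subgroups make it worse. The trial can suggest candidate factors but cannot establish a score. It can say something about UF start time only within the first 24 h.

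The overall comparison of UF with diuretics is not affected, so this is a correction that should be made rather than a flaw that undermines the trial.

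**What to change.** - In the Statistical analysis section, replace the stratified Cox and chi-square/Fisher sentences with a treatment-by-factor interaction term in whatever model is used for the primary efficacy endpoint, fitted to both arms.
- Name a small set of factors in advance. Which ones is for the investigators to decide.
- Report each interaction estimate with its 95% CI and label the analyses exploratory.
- In the abstract, change the scoring-system sentence to say that the trial will identify candidate factors for a score to be developed and validated in a later study, and bring the main Discussion into line.
- State that the trial cannot inform early-versus-late timing of UF beyond 24 h.

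The cost is wording only: no extra patients, visits or data. The downside is that the scoring-system claim is postponed, and most of the 14 factors would be reported descriptively, if at all.
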